### Data management

Data management will be applied by an electronic data capture system (EDC). Two data administrators will input and proofread the data independently. Divergences raised about the CRF and data proofread will be generated as a concentrator data ready queue (DRQ). Data administrators will send the DRQ to the researchers through the clinical supervisor. The researchers deal with the DRQ and return it as soon as possible. The data administrators will confirm the modification and enter the new data according to the responses of the researchers, and issue DRQ again if necessary. After reviewing and confirming the correctness of the database, the main researchers, applicants, and statistical analysts will lock the data. The locked data file will not be changed. Any problems found after data locking will be corrected. All research results (including personal data, laboratory test documents, CRF) appearing in the original medical records will be completely confidential to the extent permitted by law. The subject’s name will not appear in the CRF table, only the initials of the subject’s name and the number assigned when participating in the study. In relevant research summaries, articles, and public publications, if necessary, only the initials and number will appear.

### Statistical analysis

The statistical analysis will be performed by an independent statistician. After the trial protocol is determined, the statistician is responsible for formulating the detailed statistical analysis plan in consultation with the principal investigator. Statistical analysis will be conducted using the SAS version 9.1 statistical software.

The primary analyses for this study will adopt the intention-to-treat (ITT) principle. The full analysis set [41] includes participants who met the inclusion and exclusion criteria and received at least one evaluation after randomization. The per-protocol set (PPS) includes participants who had good compliance (80–120% of the trial drugs were used), did not take prohibited drugs during the trial, and completed the CRF. Safety analysis will be conducted based on a safety analysis set including participants who have received at least one intervention and safety evaluation.

Participants can withdraw at any time and will be recorded the reason for withdrawal. Participants who discontinue or deviate from intervention protocols will be informed by interviewers to get the reason for dropout. The original data of all withdrawn and terminated cases should be kept and recorded for further analysis. The last observation of participants who dropped out or existing missing data will be carried forward as the final data.

Continuous variables will be presented as mean ± standard deviation [42] or median with quartile range, according to the distribution. An independent *t*-test or the Mann-Whitney *U* test will be conducted to compare the differences between the groups. Dichotomous variables will be presented as frequency and percentage and analyzed with the chi-square test or Fisher’s exact test. Subgroup analyses will be performed based on groups with high heterogeneity if necessary.

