**Methods:**

This is a randomized, double-blind, placebo-controlled trial. A total of 210 participants will be enrolled and randomized into the QSHY or placebo granules groups in equal proportions, who will receive treatment for 24 weeks. The primary outcome will be the change in LDL-C from baseline to week 12. Secondary outcomes will be changes in other serum lipids markers, life quality measuring health surveys, and traditional Chinese medicine (TCM) pattern scale. All related tests will be measured at baseline, week 12, and week 24 after enrollment. Adverse events and the safety of intervention will be monitored and evaluated.

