### Blinding

#### Blind editing and blind bottom preservation

All patients and researchers will be blinded to the treatment assignments until the trial is completed. Personnel unrelated to this clinical trial will complete the preparation of drug blinding and emergency letters. Duplicate blinding is adopted in this study. All the data will be uploaded into the electronic database in double copies; the final statistical plan will be confirmed by question answering, verification, and blind review; and the database will be locked. After that, the first unblinding will be performed, and the results of the undefined group information corresponding to random numbers for necessary statistical analysis can be obtained. After the analysis, the main researcher will perform the second unblinding with the identification of two groups. All the unblinding processes will be recorded. In case of emergency, the reason, time, and place of blindness breaking will be recorded, and the cases will be treated as missing cases.

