### Study visit overview

The visits in this trial are designed as 5-time points during 24 weeks of intervention: baseline, 6 weeks ± 5 days after enrollment, 12 weeks ± 5 days after enrollment, 18 weeks ± 5 days after enrollment, and 24 weeks ± 5 days after enrollment. At each visit time point, participants will be tested the laboratory index or recorded vital signs according to the study schedule. The detailed flow path information is shown in Fig. 2.

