### Outcomes

The primary outcome in this study is the change in LDL-C from baseline to week 12. The secondary outcomes are the changes in fasting serum TC, TG, HDL-C, non-HDL-C, apolipoprotein (Apo) A-I, ApoA-II, ApoB, and fasting blood glucose at 12-week assessment and 24-week assessment, and the change in the ratio of TC/HDL-C at 12-week assessment and 24-week assessment. All mentioned serum biochemical markers will be measured at baseline, 12-week, and 24-week after randomization. The measurement of life quality will be assessed by the Medical Outcomes Study Item short-Form Health Survey (SF-36) questionnaire. The changes in the syndrome of TCM for participants will be measured using four TCM diagnostic methods and the Scores of TCM syndrome Scale. Other outcomes are blood pressure, heart rate, body mass index (BMI), and waist-to-hip ratio (WHR).

Safety indexes are blood and urine routine examination and results of serum liver function test including AST, ALT, alkaline phosphatase (ALP), and serum renal function test including creatinine (CR) uric acid (UA) and blood urea nitrogen (BUN). Adverse events that occurred in the trial period will be monitored at each visit. All collected adverse events and their degree will be recorded with followed medical intervention in the CRF.

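### Carrying the last observation forward sets the primary LDL-C change to exactly zero for any analysed participant without a week-12 value, because no LDL-C is scheduled between baseline and week 12

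*Protocol article*

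**What the plan says.** The Outcomes section of the protocol article states: "The primary outcome in this study is the change in LDL-C from baseline to week 12". It adds that "All mentioned serum biochemical markers will be measured at baseline, 12-week, and 24-week after randomization", and the Methods paragraph of the abstract agrees: "All related tests will be measured at baseline, week 12, and week 24 after enrollment". The Study visit overview lists visits at baseline and weeks 6, 12, 18 and 24, but the text puts no serum biochemistry at weeks 6 or 18. The study schedule figure is not available here.

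The Statistical analysis section says "The primary analyses for this study will adopt the intention-to-treat (ITT) principle". The full analysis set "includes participants who met the inclusion and exclusion criteria and received at least one evaluation after randomization"; that evaluation is not tied to LDL-C. For missing data, "The last observation of participants who dropped out or existing missing data will be carried forward as the final data". The between-group comparison is an unadjusted t-test or Mann-Whitney test. Under Blinding, after an emergency code break "the cases will be treated as missing cases".

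**The concern.** Carrying forward needs an earlier post-baseline value if it is to say anything about response to treatment. For the primary outcome there is none, so the rule becomes baseline carried forward and the change is zero by construction.

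Three kinds of participant can be affected:

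- someone seen at week 6 and then lost, who has had a post-randomization evaluation but no LDL-C;
- someone who misses week 12 but returns at week 24, whose later LDL-C is ignored in favour of baseline;
- someone treated as missing after emergency unblinding, if the rule is applied to them.

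Zero is not a neutral value in this trial. Both arms receive diet and exercise education (Interventions). The Discussion says such measures can improve the condition. The Sample size section reports a 12.71% fall in total cholesterol in an earlier control group and uses 0.155 for control in its formula. The planned tests then treat each imputed zero as a real observation. At stake are the size of the estimated effect and, if the arms lose different numbers before week 12, the direction of the bias and the false-positive rate.

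**Working it through.** **The plan's own figure first.** The stated formula with one-sided alpha 0.05 and power 80% gives
(1.645 + 0.842)² × [0.305 × 0.695 + 0.155 × 0.845] / 0.15² = 6.183 × 0.34295 / 0.0225 = 94.2, stated as 94. Then 94 / 0.90 = 104.4, rounded up to 105 per arm. Both figures reproduce.

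**Inputs from the protocol (Sample size).** 105 per arm; 10% loss, with neither arm nor timing given; 0.155 and 0.305 for control and QSHY; 12.71% control fall in total cholesterol.

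**Assumptions.** The values 0.155 and 0.305 are read as mean percentage falls in LDL-C, although the formula uses them as proportions. The SD of percentage change, which the protocol does not give, is taken as 15 to 35 points. Unless stated otherwise, all loss falls before week 12, every such participant stays in the analysis set, and loss is unrelated to the change that would have been seen.

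**Formula.** Let an arm have true mean change μ, standard deviation SD and fraction d without a week-12 value. After zeros are imputed:
- mean = (1 − d)μ
- variance = (1 − d)SD² + d(1 − d)μ²

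The rejection rate comes from a two-sided 5% z-test with 105 per arm.

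**Equal loss, 10% in each arm, true effect present.**
0.90 × 30.5 − 0.90 × 15.5 = 27.45 − 13.95 = 13.5 points, against a true 15. At SD 35, power is 0.82, against 0.84 for 94 completers per arm. With a shared fall and no true effect, the expected difference is 0 and the error rate is 5.0%.

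**Unequal loss, true effect present.**
- 15% QSHY, 5% placebo: 0.85 × 30.5 − 0.95 × 15.5 = 25.925 − 14.725 = 11.2 points.
- 5% QSHY, 15% placebo: 0.95 × 30.5 − 0.85 × 15.5 = 28.975 − 13.175 = 15.8 points, which overstates the true 15.

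**Unequal loss, no true effect.** With the same fall in both arms, 5% loss on QSHY and 15% on placebo, the spurious difference is 15.5 × (0.15 − 0.05) = 1.55 points in favour of QSHY. Reversing the split reverses the sign.

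Worked example at SD 20:
- QSHY variance: 0.95 × 400 + 0.05 × 0.95 × 15.5² = 391.4
- placebo variance: 0.85 × 400 + 0.15 × 0.85 × 15.5² = 370.6
- standard error: √((391.4 + 370.6) / 105) = 2.69
- shift: 1.55 / 2.69 = 0.575 standard errors, giving a two-sided rejection rate of 8.9%

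A simulated t-test (40,000 runs) gave 9.2% for this case.

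| Shared fall; loss QSHY / placebo | Spurious difference | Error, SD 15 | SD 20 | SD 35 |
|---|---|---|---|---|
| 15.5%; 5% / 15% | 1.55 | 11.7% | 8.9% | 6.3% |
| 12.71%; 5% / 15% | 1.27 | 9.6% | 7.6% | 5.9% |
| 15.5%; 2.5% / 7.5% | 0.78 | 6.6% | 5.9% | 5.3% |
| 0%; any split | 0 | 5.0% | 5.0% | 5.0% |

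The third row places only half of the 10% allowance before week 12 and keeps the threefold imbalance.

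**The case against.** The strongest reply is that the text does not settle who receives the zero. If the post-randomization evaluation in the full analysis set means an efficacy evaluation, the first one is week 12, and people lost earlier leave the set instead of being imputed. Carrying forward to the final data could also mean carrying week 12 to week 24, which would touch secondary outcomes only. Either reading shrinks the affected group. But the rule also covers missing data in general, so it still reaches a participant who misses week 12 and returns at week 24 and, on a plain reading, one treated as missing after a code break. A rule that needs a favourable reading of two undefined terms should be clarified anyway.

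A reader might infer that every dropout is scored as no change. The documents do not support that: anyone lost after week 12 has an observed primary value. A reader might also infer that the rule inflates the error rate in general. It does not. Inflation needs both unequal early loss and a non-zero shared change, and the protocol gives no loss by arm. If QSHY loses more participants, the bias runs against the drug.

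It is also fair that a detailed analysis plan is foreseen and may add sensitivity analyses, so their absence from the article is no fault. That does not answer the point, which concerns a rule the article states. The per-protocol set, which requires a completed CRF, is largely free of imputation but is not the primary analysis.

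Finally, a repeated-measures model has only a baseline value for those lost early, so for them it comes close to a baseline-adjusted completer analysis. That stands. Even so, the model avoids inserting zeros and uses week-24 data from those who return.

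**Conclusion.** The point holds in a limited form. As written, the rule gives a primary change of exactly zero to any full-analysis-set participant without a week-12 LDL-C, in a trial whose own planning figures expect a fall in both arms.

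With equal early loss the cost is dilution of at most 1.5 points out of 15 (10%) under the plan's allowance, and type I error is unaffected. With unequal early loss and a shared fall, the better-retained arm gains, so the rule cannot be defended as conservative. The 1.55 points and the error of about 6% to 12% are a scenario that rests on an assumed 5% versus 15% loss, all of it before week 12, and on assumed SDs. They shrink if part of the loss comes later.

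Severity is should-fix. The defect is in the stated rule, but its size depends on loss by arm, which the documents do not give.

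**What to change.** For the primary analysis, replace last observation carried forward with one of the following:

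- a likelihood-based repeated-measures model of LDL-C at weeks 12 and 24, including baseline and treatment-by-visit terms, with the week-12 contrast as the primary estimate; or
- multiple imputation of week-12 LDL-C from baseline, arm and available visits.

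Add a sensitivity analysis that imputes missing values from the placebo arm, since both methods assume that missingness is explained by the observed data. Keep last observation carried forward at most as a sensitivity analysis. State what counts as an evaluation for the full analysis set, and that membership does not depend on an imputed LDL-C. Say how emergency-unblinded cases enter the primary analysis.

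The cost is modest programming, a slightly wider confidence interval and a protocol amendment. The Ethics issue section requires renewed approval for revisions, so this is more than a wording change in the analysis plan. No new visits or blood samples are needed. The article reports 102 of 210 participants enrolled and places confirmation of the final statistical plan at blind review, so the change can be made before unblinding.

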### Participants

#### Inclusion criteria

The following are the inclusion criteria:
For patients who meet the diagnostic criteria of Chinese and Western medicine for hyperlipidemia. The diagnostic criteria for hyperlipidemia refer to the Chinese Guidelines for the Prevention and Treatment of Dyslipidemia in Adults (2016 Revised Edition) [39]. TCM diagnosis, syndrome differentiation criteria, and their basis refer to the TCM diagnosis and treatment criteria for dyslipidemia formulated by the heart disease branch of the Chinese society of TCM [40].Aged over 18 years.Participates without ASCVD, 3.4 mmol/L < LDL-C < 4.9 mmol/L; ASCVD patients, 2.6 mmol/L < LDL-C < 4.9 mmol/L.Patients with fasting TG < 5.7 mmol/L.BMI < 35 kg/m^2^.Willing and able to follow the scheduled visit plan, diet and exercise instructions, laboratory tests, and other procedures.Patients who signed informed consent.

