### Sample size

According to the previous results from a single-center clinical observation, after being treated with QSHY decoction, the fasting serum TC level decreased by 23.84% compared with baseline, and the fasting serum TC level in the control group decreased by 12.71% compared with baseline. It is expected that the decrease of fasting LDL-C level in the QSHY granule group will increase by 15% compared with placebo. Assuming *a* = 0.05, *β* = 0.2, *n*_*T*_: *n*_*C*_ = 1:1, *ẟ* = 0, *π*_*C*_ = 0.155, and *π*_*T*_ = 0.305, according to the formula of the optimal sample size, 94 samples in each group will be obtained. Considering the leakage rate of 10%, there will be at least 105 cases in each group.
$$ {n}_T={n}_C=\frac{{\left({z}_{1-\alpha }+{z}_{1-\beta}\right)}^2\left[{\pi}_T\left(1-{\pi}_T\right)+{\pi}_C\left(1-{\pi}_C\right)\right]}{{\left[\left({\pi}_T-{\pi}_C\right)-\delta \right]}^2} $$

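### The primary LDL-C change is to be compared by an unadjusted t-test or Mann-Whitney test, with neither named as primary; adjusting for the baseline LDL-C already collected would fix the effect measure and add some precision.

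*Protocol article*

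**What the plan says.** The Outcomes section defines a continuous primary endpoint: "The primary outcome in this study is the change in LDL-C from baseline to week 12". For all continuous variables, the Statistical analysis section offers an independent t-test or a Mann-Whitney U "test will be conducted to compare the differences between the groups". It names no model and no covariate, and it does not say which of the two tests is primary.

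The sentence before it describes summary statistics, as a mean with SD "or median with quartile range, according to the distribution". No separate rule for choosing the test is given.

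Baseline LDL-C is available by design: "All related tests will be measured at baseline, week 12, and week 24 after enrollment". Entry is restricted on the same variable: "Participates without ASCVD, 3.4 mmol/L < LDL-C < 4.9 mmol/L", with a wider window of 2.6 to 4.9 mmol/L for patients with ASCVD.

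The article defers detail: "the statistician is responsible for formulating the detailed statistical analysis plan in consultation with the principal investigator". The Blinding section adds that the final statistical plan is confirmed at blind review, before database lock and the first unblinding.

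**The concern.** The change score subtracts baseline with a fixed coefficient of one. When the correlation between baseline and week 12 is below one, as it is for a measured lipid, change remains negatively correlated with baseline. The unadjusted comparison leaves that part of the variance in the error term. ANCOVA estimates the coefficient and removes it. Randomisation is described without stratification on LDL-C, so a chance difference in baseline would also pass into the point estimate.

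The second issue is what gets estimated. A t-test goes with a difference in mean change. A Mann-Whitney test goes with a rank-based quantity. With both left open, the primary effect measure is not fixed.

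At stake is some precision on the primary comparison, and a primary result whose scale could be settled late.

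**Working it through.** **1. The plan's own figure.** The Sample size section states: "Assuming *a* = 0.05, *β* = 0.2". Its printed formula uses z at 1−α (one-sided), with proportions 0.305 and 0.155:

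- n = (1.645 + 0.842)² × [0.305×0.695 + 0.155×0.845] / 0.15² = 94.24, stated as 94 per arm.
- 94 / 0.90 = 104.4, so 105 per arm.

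The figure reproduces. It is built on proportions, so it contains no SD of LDL-C and no correlation. The ANCOVA gain therefore has to rest on assumptions.

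**2. Anchor for the comparison.** Assume a mean effect at which the unadjusted t-test on change has 80% power with 94 per arm, two-sided 0.05. The standardised signal is 1.960 + 0.842 = 2.802. This is a hypothetical reference point, not the trial's planned power.

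**3. Variance ratio.** Let ρ be the baseline to week-12 correlation before selection, with equal SDs before selection. Let k be the fraction of the baseline variance left after the entry window is applied. With a linear regression of week 12 on baseline:

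- Variance of change ∝ (1−ρ)²k + (1−ρ²)
- Residual variance under ANCOVA ∝ (1−ρ²)
- Ratio R = (1+ρ) / [(1−ρ)k + (1+ρ)]
- Power = Φ(2.802/√R − 1.960)

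Without truncation k = 1, and R reduces to (1+ρ)/2.

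**4. Value of k for the 3.4-4.9 window.** Assume a normal source with mean 3.6 and SD 0.8 mmol/L. The limits are a = (3.4−3.6)/0.8 = −0.25 and b = (4.9−3.6)/0.8 = 1.625. The probability inside is 0.547. The truncated-normal variance formula gives k = 1 − 0.494 − 0.263 ≈ 0.244.

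**5. Results.**

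| ρ | R, k = 1 | ANCOVA power | R, k = 0.244 | ANCOVA power |
|---|---|---|---|---|
| 0.3 | 0.65 | 93.5% | 0.884 | 84.6% |
| 0.4 | 0.70 | 91.8% | 0.905 | 83.8% |
| 0.5 | 0.75 | 89.9% | 0.925 | 83.0% |
| 0.7 | 0.85 | 86.0% | 0.959 | 81.6% |
| 0.9 | 0.95 | 82.0% | 0.987 | 80.5% |

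In patients, 1/R in the truncated case is 1.13 down to 1.01, so 13% to 1% more patients. In the equal-variance case at ρ = 0.4 to 0.7 it is 1.43 to 1.18.

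**6. Simulation with the truncated baseline** (3,000 runs per ρ, normal errors, ρ 0.3 to 0.9): ANCOVA about 79% to 84%, t-test 79% to 80%, Mann-Whitney 77% to 78%. This agrees with the formula within simulation error.

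**7. Sensitivity to the assumed source.**

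- Moving the source mean over 3.3 to 4.0 and the SD over 0.6 to 1.0 takes k from 0.16 to 0.42. The most favourable corner (mean 4.0, SD 0.6, ρ = 0.3) gives R = 1.3/(0.7×0.416 + 1.3) = 0.82 and power of about 87%. The least favourable (mean 3.3, SD 1.0, ρ = 0.9) gives R = 0.99 and power of about 80%.
- For the wider ASCVD window (2.6 to 4.9, mean 3.6, SD 0.8), k = 0.52, R is 0.78 to 0.97, and power is 89% to 81%.

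**The case against.** **The unadjusted test is valid.** This stands. Under 1:1 randomisation, regression to the mean acts on both arms alike, and chance baseline imbalance is already allowed for in the standard error. A reader might infer from the LDL-C entry window that the comparison is biased. The documents do not support that.

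**The test is not shown to be picked after seeing results.** This also stands. A reader might infer a data-driven choice from the reference to the distribution. Grammatically, those words govern the descriptive summary. The Blinding section has the plan confirmed at blind review, and the first unblinding shows only unidentified groups. A choice made then would not be steered by treatment. What remains is that the article states no selection rule and no primary effect measure.

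**The detail belongs in the SAP.** This stands in part. The SAP is not shown and may already settle the matter. But the article is not silent: it names a method, and that method is unadjusted and two-way. Improving a stated choice differs from asking for missing detail.

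**The gain may be small.** This stands. The (1+ρ)/2 formula needs equal variances at baseline and week 12, and a narrow entry window works against that. With strongly skewed or heavy-tailed changes, the rank test could match or beat ANCOVA, which is a reason to keep it as a sensitivity analysis.

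**Conclusion.** The point holds as a low-cost improvement, not as an error. The stated primary comparison is valid, but it does not use the baseline LDL-C already in hand, and it does not fix whether the result is a mean difference or a rank comparison.

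The size is modest and rests on assumptions. If the unadjusted test had 80% power at 94 per arm (two-sided 0.05), ANCOVA would have about 80% to 85% with baseline confined to 3.4-4.9 mmol/L, for an assumed source mean of 3.6, SD of 0.8 and correlation of 0.3 to 0.9. Other plausible source values stretch the top to about 87%. The range 86% to 92% applies only with equal variances and correlation 0.4 to 0.7, and should be read as an upper scenario rather than the expected gain. At high correlation with a narrow baseline range, the gain is close to nil. None of the cases checked shows a material loss from adjusting. The case for fixing the effect measure in advance does not depend on these figures.

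**What to change.** Before the first unblinding, and preferably before blind review, name one primary analysis: ANCOVA of the LDL-C change to week 12, with treatment and baseline LDL-C as terms. Report the adjusted mean difference with its 95% CI. Keep the Mann-Whitney test as a sensitivity analysis. The same model can serve the other lipid changes.

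An indicator for the ASCVD entry window is optional. The exclusion criteria remove patients at high or very high risk of arteriosclerotic cardiovascular disease, so few patients with ASCVD may enter and the term may be sparse.

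The cost is wording in the SAP and one degree of freedom. No further data, visits or patients are needed. If the change is made in the protocol itself, the Ethics issue section requires reapproval by the ethics committee. The article reports 102 patients enrolled with recruitment still open, so at that date there was time to make the change.
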